#### **12.1.2 Progression-free survival (PFS)**

According to RECIST 1.1, PFS is defined as the time from the treatment initiation to the first occurrence of investigator-assessed objective tumor progression or death. In the absence of PD, even if the patient has discontinued aumolertinib treatment or received another anti-cancer treatment before PD, his/her imaging tumor evaluation should still be collected until RECIST-defined PD. Symptomatic deterioration is not considered a progression event.

Subjects who have not progressed or died at the time of analysis will be censored at the last date of their last RECIST assessment. If a subject has PD or dies after 2 or more missing visits, he/she will be censored at the last date of his/her last RECIST assessment. PFS-derived data are based on assessment date rather than visit date.

Systemic PFS and iPFS will be assessed separately:

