**Figure 1. Schematic overview of the study**

• **Screening period (D–28 to D–1)**

Inpatients or outpatients will be screened after signing the informed consent form and undergo relevant laboratory tests and assessments. Subjects who meet all the inclusion criteria and do not meet any of the exclusion criteria may be enrolled.

• **Treatment period (C1+, D1+)**

High-dose aumolertinib group: Oral administration of 165 mg aumolertinib tablets once daily (55 mg/tablet, 3 tablets/day).

Each treatment cycle consists of 28 days of continuous administration. After treatment is started, efficacy will be evaluated once every 8 weeks as per RECIST 1.1. Patients will continue treatment until progressive disease assessed by investigator per RECIST 1.1 or until the withdrawal or discontinuation criteria are met. Patients may continue to receive the treatment even if progressive disease per RECIST 1.1 occurs as long as they still benefit from the treatment as judged by investigator (see Section 12.1.3 or 9.1.3.4 for details); if it is decided to continue the treatment, the baseline and follow-up plan will not be affected by the additional courses of treatment. Once the treatment is discontinued due to lack of clinical benefit upon judgment, it cannot be started again.

• **Follow-up period**

Subjects who discontinue the treatment due to meeting the discontinuation criteria should complete the treatment discontinuation follow-up, the 28-day safety follow-up after treatment discontinuation, and survival follow-up once every 12 weeks as specified in the study plan.

Subjects without progressive disease at treatment discontinuation will be followed up once every 8 weeks until progressive disease assessed by investigator per RECIST 1.1 (intracranial, extracranial, and systemic), even if the subject has received other anti-tumor treatments; after progressive disease, the subjects will be followed up for survival once every 12 weeks as specified in the study plan.

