- Baseline tumor assessment: Contrast-enhanced CT of the chest, contrast-enhanced CT of the abdomen (including liver and adrenal glands), contrast-enhanced MRI (preferred)/contrast-enhanced CT of the head, bone scan, and imaging examination of other sites with indications for metastasis. The slice thickness in a CT scan must be  $\leq 5$  mm. The results of contrast-enhanced CT of the chest, contrast-enhanced CT of the abdomen (including the liver and adrenal glands), and contrast-enhanced MRI (preferred)/contrast-enhanced CT of the head obtained within 28 days prior to the enrollment are acceptable. Bone scan results obtained within 3 months prior to the enrollment are acceptable and are not subject to the time of providing informed consent. Patients who are allergic to contrast agents should undergo a plain chest CT and should have MRI scans of the abdomen and head. If suspected metastases are found on a bone scan, bone metastases must be confirmed by CT, MRI, or X-ray. If a PET-CT scan (slice thickness must be  $\leq 5$  mm) is conducted within 3 months prior to enrollment, a bone scan will be unnecessary.
- Evaluation of inclusion and exclusion criteria
- Recording of AEs and concomitant medications (concomitant medications started from 4 weeks before enrollment)

It is recommended that the screening process should start with the confirmation of EGFR mutation status.

If a laboratory test value is abnormal in the screening period and no corrective treatment is needed as judged by the investigator, a re-test may be performed within 1 week; if a re-test is performed, the re-test results should be used as the basis for judgment against the inclusion/exclusion criteria. If the corrective treatment is needed as judged by the investigator, the eligible test results obtained after corrective treatment should remain stable for at least 1 week and meet the requirements for the time window in the screening period and the sponsor's requirements.

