**Table 3. Determination of disease progression, subsequent anti-tumor therapies, and data collection**

| Systematic review | Intracranial lesions | Extracranial lesions | Subsequent treatment                                                   | Subsequent anti-tumor evaluation                                                                               |
|-------------------|----------------------|----------------------|------------------------------------------------------------------------|----------------------------------------------------------------------------------------------------------------|
| PD                | PD                   | PD                   | Treatment discontinuation                                              | Continue evaluation until progressive disease as per RECIST 1.1 (all intracranial, extracranial, and systemic) |
| PD                | PD                   | Non-PD               | Treatment discontinuation                                              |                                                                                                                |
|                   |                      |                      | Continue aumolertinib + brain local treatment                          |                                                                                                                |
| PD                | Non-PD               | PD                   | Treatment discontinuation                                              |                                                                                                                |
|                   |                      |                      | Continue aumolertinib + extracranial local treatment (oligometastasis) |                                                                                                                |
| Non-PD            | PD                   | PD                   | Treatment discontinuation                                              |                                                                                                                |
| Non-PD            | PD                   | Non-PD               | Treatment discontinuation                                              |                                                                                                                |

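### Section 12.1.2 censors PD after two or more missed visits at the last RECIST assessment without saying before the gap, so as written a known progressor counts as progression-free up to or past the PD scan

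*Protocol*

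**What the plan says.** Section 12.1.2 defines the PFS event as "the first occurrence of investigator-assessed objective tumor progression or death", measured from treatment initiation, and adds that "PFS-derived data are based on assessment date rather than visit date". Two censoring rules follow:

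- Without an event: "Subjects who have not progressed or died at the time of analysis will be censored at the last date of their last RECIST assessment".
- With an event after a gap, that is, when a patient "has PD or dies after 2 or more missing visits, he/she will be censored at the last date of his/her last RECIST assessment".

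Both rules use the same anchor, the last RECIST assessment. Neither mentions the last assessment before the missed visits, and no other section supplies such a cut-off. The second rule also does not say that the missed visits must be consecutive.

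The definitions of systemic PFS and iPFS take over the same principles. Section 12.1.4 ties the end and the censoring of DoR to the PFS dates.

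Scanning need not stop at the first PD. Table 3 in Section 9.1.3.4 requires sites to "Continue evaluation until progressive disease as per RECIST 1.1 (all intracranial, extracranial, and systemic"). Where treatment goes on after PD, Section 6.1 says that "if it is decided to continue the treatment, the baseline and follow-up plan will not be affected by the additional courses of treatment".

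The primary analysis (Section 12.4.2.1) is the Kaplan-Meier 12-month PFS rate. Section 5.3 sets the null at 40% and the alternative at 60%.

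**The concern.** A missed-visit rule normally goes back to the last scan at which the patient was known to be progression-free. This one goes to the patient's last scan of any kind. For a progressor that scan shows PD or comes after it.

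The patient is then credited with progression-free time through an interval in which nobody looked, up to or beyond a documented progression, and contributes no event. The trial has one arm and a fixed 40% null, so no comparator can absorb the bias. A SAP that copies the sentence inherits the fault, and one that corrects it departs from the protocol.

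**Working it through.** **1. One patient, two readings.** The visit schedule in Appendix B, note a, is weeks 4, 12 and then every 8. Take scans without PD at weeks 4, 12 and 20, weeks 28 and 36 missed, and PD at week 44.

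| Reading | Censored at |
|---|---|
| Last assessment before the gap | week 20 |
| As written, PD in all compartments at week 44 | week 44 |
| As written, PD in one compartment only, scanned again at week 52 | week 52 |

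The literal reading adds 44 − 20 = 24 weeks, or 52 − 20 = 32 weeks, of progression-free time.

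**2. Direction.** The Kaplan-Meier estimate is a product of factors 1 − d/r, with d events among r at risk.

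- Keeping a censored patient at risk longer turns r into r + 1 at each event time in the added interval. Since 1 − d/(r + 1) > 1 − d/r when d > 0, the 12-month estimate can only stay the same or rise.
- Compared with counting the PD as an event, d also loses one, which raises the estimate again.

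The direction therefore does not depend on how many patients are affected.

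**3. Size.** The point disputes no figure in the protocol, so the check starts from its 40% and 60%. Assumptions not in the protocol:

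- PFS is exponential with S(12 months) = 0.40 or 0.60, so the weekly hazard is −ln(S)/52.18.
- A share q of progressors misses the two scans immediately before the PD scan.
- There is no other censoring.

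The rows for q = 5% and 10% use 200,000 simulated patients. The 15% rows use 1,000,000 under the same specification. With q = 0 every rule returns 40.0% and 60.0%, as it should.

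| True rate | q | PD counted as event | Censored before gap | As written, at PD scan | As written, one scan later |
|---|---|---|---|---|---|
| 40% | 5% | 40.8 | 41.9 | 42.6 | 42.8 |
| 40% | 10% | 41.6 | 43.8 | 45.2 | 45.6 |
| 40% | 15% | 42.1 | 45.7 | 47.8 | 48.3 |
| 60% | 5% | 60.6 | 61.6 | 61.9 | 62.0 |
| 60% | 10% | 61.1 | 63.1 | 63.7 | 63.9 |
| 60% | 15% | 61.7 | 64.7 | 65.6 | 65.8 |

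The effect of the wording is the as-written column minus the pre-gap column:

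- True rate 40%: 42.6 − 41.9 = 0.7 points at q = 5%, and 47.8 − 45.7 = 2.1 at q = 15%. With a later scan, 48.3 − 45.7 = 2.6.
- True rate 60%: 61.9 − 61.6 = 0.3 points at q = 5%, and 65.6 − 64.7 = 0.9 at q = 15%. With a later scan, 65.8 − 64.7 = 1.1.

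**4. What the wording does not cause.** Pre-gap censoring already lies above event counting: 41.9 − 40.8 = 1.1 points at q = 5% and 45.7 − 42.1 = 3.6 at q = 15% (true rate 40%). The event-counted column is itself above 40% because the assumed gap delays detection by two scans.

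**5. Scale.** With the planned 63 patients, the binomial standard error at 40% is √(0.4 × 0.6/63) = 0.062, or 6.2 points. The wording effect at that rate is 0.7/6.2 ≈ 0.1 to 2.6/6.2 ≈ 0.4 of a standard error.

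**The case against.** The strongest defence is that the intent is easy to guess. A missed-visit clause that censors at the PD scan would serve no purpose, so a competent programmer would use the last scan before the gap, and the SAP, which was not available, may say so. Part of this stands: the fault is one of drafting, and harm follows only if the sentence is coded as it reads. But the protocol chose to state the rule, and the sentence before it uses the same phrase to mean the most recent scan. Nothing in the document points to the guessed reading.

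The objection also rightly limits the point. A reader might infer four stronger claims that the protocol does not support:

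- *That deaths are mishandled in the same way.* For a death after a gap with no scan in between, the last RECIST assessment already precedes the gap. Censoring such deaths is an explicit choice in Section 12.1.2.
- *That impossible survival times distort the result.* For head MRI/CT and chest and abdominal CT, Section 9.1.1 accepts baseline results "obtained within 28 days prior to the enrollment are acceptable", so a patient with no post-baseline scan could receive a negative PFS time. Censoring there or at Day 1 removes the patient before any event, and the 12-month estimate is the same.
- *That the whole gap between the as-written and event-counted results is due to the wording.* Most of it comes from censoring after a gap at all, plus the assumed detection delay.
- *That every such patient is carried past PD.* A scan after PD arises only when compartments are discordant. Otherwise the censoring date is the PD scan itself.

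**Conclusion.** The point holds for PD after a gap. As written, the rule for the sole primary endpoint keeps a known progressor at risk as progression-free up to the PD scan or a later one and then drops the event, which favours the drug. iPFS, DoR and iDoR inherit it.

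Under exponential PFS, the Appendix B schedule and 5% to 15% of progressors with a two-scan gap just before PD, the wording adds about 0.7 to 2.1 points over pre-gap censoring at a true rate of 40%, and up to about 2.6 with a later scan. At 60% it adds about 0.3 to 1.1 points, the upper end being with a later scan. The affected share is an assumption and applies to progressors, not to all patients. The size moves with it; the direction does not.

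This is modest against a standard error of about 6 points. It is still a one-sided error in the primary endpoint that one sentence removes, so it should be corrected before the analysis.

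**What to change.** Replace the sentence in Section 12.1.2 with:

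*If PD or death occurs after 2 or more consecutive missed assessments, the patient is censored at the last evaluable RECIST assessment before the first missed assessment (Day 1 if there is no evaluable post-baseline assessment).*

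Carry the same text through to iPFS, DoR and iDoR.

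Add one Kaplan-Meier sensitivity analysis of the 12-month PFS rate that counts these PDs and deaths as events on their documented dates. It is needed because pre-gap censoring also raises the estimate.

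The cost is one sentence, one extra run and a possibly slightly lower reported rate. Visits, sample size and patient care do not change.

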#### **Systemic progression-free survival (PFS):**

Systemic PFS is defined as the time from the treatment initiation to the first documentation of systemic PD or death due to any cause, with other principles as above.

#### **Intracranial progression-free survival (iPFS):**

iPFS is defined as the time from the treatment initiation to the first documentation of intracranial PD or death due to any cause, with the same principles as above.

#### **12.1.3 Objective response rate (ORR)**

As per RECIST 1.1, systemic ORR is defined as the percentage of patients with at least 1 CR or PR before PD. Data until PD or last evaluable data in the absence of PD will be recorded in the assessment of ORR. However, any CR or PR that occurs after discontinuation of the study treatment and further anti-tumor treatment will not be included in the calculation of ORR.

Objective response rate will be assessed separately for intracranial lesions (iORR) and systemic lesions (ORR).

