## **7.0 SCREENING OF SUBJECTS**

### **7.1 Inclusion Criteria**

A subject must meet all the following inclusion criteria in order to be enrolled in this study:

1. Age  $\geq 18$  years old.
2. Histologically or cytologically confirmed NSCLC, which is confirmed by imaging as advanced NSCLC with brain metastases (including stage IV patients who are newly diagnosed or have relapsed after previous surgical treatment; according to the AJCC 8th edition lung cancer staging criteria).
3. Confirmed as EGFR-sensitive mutations in tumor tissue samples or blood samples by local laboratory (including exon 19 deletion or L858R, either existing alone or co-existing with other EGFR site mutations). If tumor tissues are available, the tumor tissue is recommended for testing; if tumor tissues are not available or the patient cannot undergo tissue biopsy, blood samples may be tested.
4. Have not received any systemic treatment after the diagnosis of NSCLC with metastases to brain parenchyma. For patients who have received local treatment, the lesion within the scope of the local treatment cannot be used as the target lesion unless the lesion has progressed.
5. Patients with at least 1 extracranial target lesion (measurable lesions that have not undergone local treatment such as irradiation or have shown definitive after local treatment, with a baseline longest diameter  $\geq 10$  mm (or  $\geq 15$  mm for lymph nodes)) and at least 1 intracranial lesion (with a baseline longest diameter  $\geq 5$  mm).
6. The brain condition is stable or that were controlled with anticonvulsants or dexamethasone at a maximum dose of 5 mg daily before the study treatment.
7. An Eastern Cooperative Oncology Group (ECOG) performance status score of 0 or 1, with no worsening over at least 2 weeks before study treatment, and a minimum expected survival of 3 months.
8. Female patients of childbearing potential are willing to take appropriate contraceptive measures and should not breastfeed from signing the informed consent to 6 months after the last dose of study treatment; male patients are willing to take barrier contraception (i.e., condoms) from signing the informed consent to 6 months after the last dose study treatment.
9. Female patients of childbearing potential must have a negative serum or urine HCG test within 7 days before enrollment in the study, and they must be non-lactating.
10. The subject voluntarily participates and signs the informed consent form in writing.

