response (PR), stable disease (SD), and progressive disease (PD). The analysis of the primary endpoint of this study will be based on the tumor response assessment made by the investigator as per RECIST 1.1, and the investigator will also manage the subjects based solely on the assessment results, unless medically contraindicated or faced with force majeure factors (such as update of the examination instrument by the study site). Baseline CT or MRI assessments of the chest, abdomen, and brain tissues must be performed within 28 days before the start of study treatment (not subject to the time of signing the ICF), and should be performed as close as possible to the start of study treatment. The investigator should perform additional imaging examinations based on subjects' signs and/or symptoms. The subsequent follow-up assessments should be performed using the method (CT/MRI) that is the same as that for baseline assessment. All enrolled subjects must have brain metastases as target lesions, and baseline imaging assessment of the brain must be performed, with MRI (enhanced) as the preferred examination method. Bone scans should be performed if there are indications for bone metastases (results within 3 months are acceptable), and positive sites found by bone scans should be confirmed by CT/MRI/X-ray. Only confirmed lesions can be recorded as non-target lesions. Subsequently, the bone metastases should be followed up by the same examination method as at baseline. During the study, bone scans may be added as needed. During the treatment period, tumor response assessment will be performed once every 8 weeks ( $\pm 1$  week) until progressive disease assessed by investigator per RECIST 1.1 (see Section 12.1.3 or 9.1.3.4). Tumor assessments should be performed according to the study plan whenever possible. If subjects are assessed at a time point beyond the scheduled time window ( $\pm 1$  week) and no progressive disease occurs, they should undergo subsequent assessments at the pre-specified time points whenever possible while continuing study treatment. If tumors are suspected at any other sites, the corresponding imaging examinations should be performed at the relevant sites. To achieve progression on the basis of the non-target lesion(s), there must be an overall level of substantial worsening in non-target lesion(s) such that, even in the presence of SD or PR in the target lesion(s), the overall tumor burden has increased sufficiently to merit discontinuation of treatment. A modest increase in the size of one or more non-target lesions is generally not sufficient to qualify for progression; therefore, it is uncommon to define overall tumor progression only with changes in non-target lesions in the face of SD or PR of target lesions. At each visit, objective tumor response will be assessed as per RECIST 1.1, and classified into CR, PR, SD, and PD. For the assessment of target lesion progression, the smallest lesion size in the entire course of treatment should be taken as reference, and an increase meeting the criteria will qualify for PD. If no progressive disease occurs, tumor response (CR and PR) and stable disease (SD) should be evaluated taking baseline lesion(s) as reference.

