| Comments                             | 
a. Subjects will be followed up at Week 4, Week 12, and every 8 weeks thereafter, and the efficacy should be confirmed as soon as possible for patients with PR/CR at Week 4.
 
b. Subjects should complete the visit procedures within 28 days (+7 days) after discontinuation of IMP, and ongoing and new AEs should be followed up. All AEs should be followed up until recovery or returning to the baseline level, or loss to follow-up or death of the subject. After the end of the safety follow-up period, only SAEs considered related to aumolertinib or study procedures will be collected.
 
c. A cycle is defined as 28 consecutive days of treatment.
 
d. At baseline, this evaluation should be completed before administration on the visit day. If the screening examinations are completed within 7 days before the first dose of the IMP, they can be exempted on C1D1.
 
e. Venous blood sampling: Blood samples will be collected at the following points: within <math>\pm 7</math> days before C1D1 and C2D1 administration, and within 1 week after PD (24 h after the previous dose).
 
f. Tumor tissue slice collection: 10–15 histopathological slices need to be collected before C1D1 administration and within one week after PD (24 h after the previous dose)
 
g. An ECG will be performed at the time of any cardiac-related AE.
 
h. Baseline examinations should be performed within 28 days prior to the first dose. After the start of treatment, subjects will be evaluated once every 8 weeks until PD is confirmed as per RECIST 1.1, even if the subjects discontinue the treatment or receive other anti-tumor treatments before PD. Tumor assessment data will be obtained from CT or MRI (contrast-enhanced CT or MRI is recommended as the preferred method).
 |  |  |  |  |  |                                                     |   |

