**Table 2. Overall response of target lesions**

|                                 |                                                                                                                                                                                                                                                                                            |
|---------------------------------|--------------------------------------------------------------------------------------------------------------------------------------------------------------------------------------------------------------------------------------------------------------------------------------------|
| Complete response (CR)   | Disappearance of all target lesions from baseline. Any pathological lymph nodes selected as TLs must have a short axis of $< 10$ mm.                                                                                                                                                       |
| Partial response (PR)    | At least a 30% decrease in the sum of diameters of TLs, taking as reference the baseline sum diameters.                                                                                                                                                                                    |
| Stable disease (SD)      | Neither sufficient shrinkage to qualify for PR nor sufficient increase to qualify for PD.                                                                                                                                                                                                  |
| Progressive disease (PD) | At least a 20% increase in the sum of diameters of TLs, taking as reference the smallest sum on study (this includes the baseline sum if that is the smallest on study). In addition to the relative increase of 20%, the sum must also demonstrate an absolute increase of at least 5 mm. |
| Inevaluable (NE)         | Only relevant TLs are not assessed or not evaluable or have lesion intervention.
Note: If the sum of diameters meets the criteria of PD, the lesion is not inevaluable and should be classified as a PD.                                                                                |

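### Section 12.1.3 counts a single unconfirmed CR or PR as a response for ORR and iORR and makes no use of the Week-4 confirmation in Appendix B; with 5 mm brain targets, reading error may add false intracranial responders

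*Protocol*

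**What the plan says.** - **Responder rule.** Section 12.1.3: "systemic ORR is defined as the percentage of patients with at least 1 CR or PR before PD". It continues: "Objective response rate will be assessed separately for intracranial lesions (iORR) and systemic lesions (ORR"). It gives no confirmation, interval or minimum change, and no separate rule for iORR.
- **Confirmation elsewhere.** Appendix B, comment a: "the efficacy should be confirmed as soon as possible for patients with PR/CR at Week 4". It sets no interval and does not say what follows if confirmation fails.
- **Brain lesion size.** Section 7.1, criterion 5, requires "at least 1 intracranial lesion (with a baseline longest diameter" of 5 mm or more). Section 10.2.1: "All enrolled subjects must have brain metastases as target lesions". Section 9.1.3.4 asks for one or more intracranial targets within the five-lesion cap and scores intracranial response on those same lesions.
- **Appendix D on size.** Sections 2.1, 2.4 and 4.2.1 restrict target lesions to measurable ones, at least 10 mm for non-nodal lesions, with no exception for brain.
- **Response thresholds.** Appendix D, Table 2, defines PR as "At least a 30% decrease in the sum of diameters of TLs, taking as reference the baseline sum diameters". For PD, beyond the 20% increase, "the sum must also demonstrate an absolute increase of at least 5 mm". PR has no such minimum.
- **Analysis sets.** Section 12.4.1 analyses efficacy in the FAS (main) and in the cEFR, the patients with a measurable brain lesion.

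**The concern.** The trial is open-label, single-arm and read by the investigator, so no control arm offsets false responders. A rule that accepts any one qualifying scan gives each patient several chances to be called a responder, and the chance of a false call grows with the number of scans. Comment a suggests that the authors wanted some confirmation, but the derivation does not carry it through.

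The brain is where this bears most. If the only intracranial target may be 5 mm, the PR threshold falls to a change of 1.5 mm. PD has a safeguard against small absolute changes; PR has none. A falsely called responder raises iORR and also enters iDoR, because section 12.1.4 starts the clock when PR or CR is first met.

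**Working it through.** The protocol states no figure for reading error or false response, so there is nothing of its own to reproduce.

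**Step 1: threshold.** The decrease needed for PR is 0.30 × baseline sum.
- One 5 mm lesion: 0.30 × 5 = 1.5 mm (PR at 3.5 mm or less).
- One 7 mm lesion: 2.1 mm.
- A 10 mm sum (one 10 mm lesion or two of 5 mm): 3.0 mm.
- A 15 mm sum: 4.5 mm.

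So 1.5 mm is the extreme case, not the typical one.

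**Step 2: one scan.** Assume that the true size D does not change and that readings have independent normal errors with SD s. PR is called if the follow-up reading is at most 0.7 × the baseline reading. Before selection on the baseline reading:

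P = Φ(−0.3D / (s√(1 + 0.7²))) = Φ(−0.3D / (s√1.49))

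For D = 5 mm and s = 1.0 mm: Φ(−1.5/1.22) = 11.0%. For D = 10 mm and s = 1.0 mm: Φ(−3.0/1.22) = 0.7%. Keeping only baseline readings of 5 mm or more, as entry requires, raises the 5 mm figure to 19.2%, because lesions over-read at baseline are the ones admitted.

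**Step 3: repeated scans.** Simulation of 400,000 lesions per cell, no true change, true size uniform in the stated range, baseline reading at least 5 mm. Confirmed means PR at two consecutive scans. The SD values are assumptions.

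| Intracranial targets | SD (mm) | Any PR, 4 scans | Confirmed PR, 4 scans |
|---|---|---|---|
| one, 5-10 mm | 0.5 | 0.4% | <0.1% |
| one, 5-10 mm | 0.75 | 4.6% | 0.4% |
| one, 5-10 mm | 1.0 | 13.9% | 1.8% |
| two, 5-10 mm | 1.0 | 2.8% | 0.2% |
| one, 5-7 mm | 0.5 | 0.9% | <0.1% |
| one, 5-7 mm | 1.0 | 26.2% | 4.2% |
| one, 10-15 mm | 1.0 | 0.7% | <0.1% |

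On Appendix B's visits (Weeks 4, 12, then every 8 weeks) there are 7 scans by Week 52. One 5-10 mm target at SD 1.0 mm then gives about 20% for any PR and about 3% confirmed.

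**Step 4: is confirming Week 4 alone enough?** No. For an unchanged 5 mm lesion at SD 1.0 mm over 7 scans, confirming only the Week-4 response lowers the chance of ever being called PR from 69.1% to 64.4%. Requiring two consecutive PRs at any time lowers it to 19.7%.

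**Step 5: effect on the overall iORR.** False responders can arise only among true non-responders. As an illustration, take the 60.9% CNS ORR that section 4.2.4 gives for 110 mg in second line. Non-responders are then 39.1%, and at SD 1.0 mm over 4 scans 0.391 × 13.9% = 5.4 points, or 0.054 × 63 = 3.4 patients, if every patient had one small target. At SD 0.5 mm it is 0.391 × 0.4% = 0.2 points.

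**The case against.** - **The 5 mm premise is disputed within the protocol.** Under Appendix D a 5-9 mm brain lesion is non-target, and its Table 3 has no PR category for non-target lesions, so a 1.5 mm iPR could not occur. This stands: the small-lesion part is conditional on the body text prevailing. The missing confirmation in 12.1.3 does not depend on it.
- **The noise figures are assumptions.** A reader might infer that measurement noise by itself creates intracranial responders in this trial. The documents do not support that. They give no reading SD and no distribution of lesion size or number; at SD 0.5 mm the effect is negligible, and a second target shrinks it sharply.
- **Some protection exists.** Appendix D assigns 5 mm to a faint lesion too small to measure. Where that applies, PR needs a baseline of at least 5/0.7 = 7.1 mm. It does not cover accurate readings below 5 mm, which are recorded as read.
- **Slice thickness.** A reader might add that CT slices of up to 5 mm make a 1.5 mm change unreadable. Enhanced MRI is preferred for the head and patients who cannot tolerate MRI are excluded, so this argument is weak.
- **A size split is nearly there.** With Appendix D's definition, the cEFR already holds patients with a brain lesion of 10 mm or more. This stands, and no further subgroup is needed.
- **It belongs in the SAP.** Supportive displays do. The responder rule does not, because section 12.1.3 fixes it.
- **The consequences are limited.** iORR is one of four intracranial secondary endpoints and is reported as a percentage with a 95% CI. This stands.

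**Conclusion.** The point holds in a limited form. Section 12.1.3 accepts one unconfirmed CR or PR for both ORR and iORR and is not reconciled with Appendix B, comment a; that follows from the text alone. Under the body text's 5 mm rule, reading error can add false iPR: roughly 0.4%, 5% and 14% of unchanged single 5-10 mm targets over 4 scans at assumed SDs of 0.5, 0.75 and 1.0 mm, and about 3% at 1.0 mm with two targets. These rates apply only to patients without a true response, so the inflation of iORR is smaller. Under Appendix D's 10 mm rule it is under 1% at SD 1.0 mm over 4 scans.

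ORR, iORR, DoR and iDoR are affected. Disease control hardly changes, since an unchanged lesion is already SD, and the primary 12-month PFS rate is not touched. It should be corrected, but it does not threaten the main result.

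**What to change.** 1. In section 12.1.3, define ORR and iORR as CR or PR confirmed at an assessment at least 4 weeks later, before PD or new anti-tumor treatment. The next scheduled scan suffices: the interval is 8 weeks in the body text and 6 weeks in Appendix D, section 4.1, and with ±7-day windows at both scans even 6 weeks leaves 4.
2. Align Appendix B, comment a, with this rule, so that confirmation applies to a response at any visit and its result enters the derivation.
3. Report unconfirmed ORR and iORR as supportive.
4. Reconcile the 5 mm rule (sections 7.1 and 10.2.1) with the 10 mm rule (Appendix D, sections 2.1, 2.4 and 4.2.1), so that intracranial target and cEFR each have one meaning. If the cEFR uses 10 mm, no extra size-split analysis is needed.

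The cost is wording only, as the scans are already scheduled. ORR and iORR will be slightly lower, and a responder with no later scan counts as unconfirmed.
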